## Abstract

**Background:**

The incidence of chronic diseases, including diabetes mellitus (DM), heart failure (HF) and chronic obstructive pulmonary disease (COPD) is on the rise. The existing health care system must evolve to meet the growing needs of patients with these chronic diseases and reduce the strain on both acute care and hospital-based health care resources. Paramedics are an allied health care resource consisting of highly-trained practitioners who are comfortable working independently and in collaboration with other resources in the out-of-hospital setting. Expanding the paramedic’s scope of practice to include community-based care may decrease the utilization of acute care and hospital-based health care resources by patients with chronic disease.

**Methods/Design:**

This will be a pragmatic, randomized controlled trial comparing a community paramedic intervention to standard of care for patients with one of three chronic diseases. The objective of the trial is to determine whether community paramedics conducting regular home visits, including health assessments and evidence-based treatments, in partnership with primary care physicians and other community based resources, will decrease the rate of hospitalization and emergency department use for patients with DM, HF and COPD. The primary outcome measure will be the rate of hospitalization at one year. Secondary outcomes will include measures of health system utilization, overall health status, and cost-effectiveness of the intervention over the same time period. Outcome measures will be assessed using both Poisson regression and negative binomial regression analyses to assess the primary outcome.

**Discussion:**

The results of this study will be used to inform decisions around the implementation of community paramedic programs. If successful in preventing hospitalizations, it has the ability to be scaled up to other regions, both nationally and internationally. The methods described in this paper will serve as a basis for future work related to this study.

**Trial registration:**

ClinicalTrials.gov: NCT02034045. Date: 9 January 2014.

**Electronic supplementary material:**

The online version of this article (doi:10.1186/1745-6215-15-473) contains supplementary material, which is available to authorized users.

## Background

Patients with chronic diseases have high rates of health care utilization and are currently costing the health care system billions of dollars each year [1–3]. In order to effectively care for the increasing number of individuals living with chronic disease, there has emerged a need for novel community-based health initiatives. Individuals with diabetes mellitus (DM) are over 3 times more likely to be hospitalized with cardiovascular disease than individuals without diabetes, 12 times more likely to be hospitalized with end-stage renal disease, and almost 20 times more likely to be hospitalized with non-traumatic lower limb amputations [4]. There are 5.5 million people in the United States and Canada living with heart failure (HF) with 850,000 new patients diagnosed annually [5, 6] and more than 900,000 hospitalizations a year are attributable to HF [6–8]. Chronic obstructive pulmonary disease (COPD) is one of the fastest growing chronic diseases; it is the third leading cause of death in the United States [9] and fourth leading cause of death in Canada, [10] and has an average hospitalization of 10 days for an exacerbation with an associated cost of $10,000 [11]. The existing health care system, which primarily revolves around hospital-based care and primary care providers, must evolve to incorporate new strategies of delivering care to better meet the needs of this growing population, resulting in improved patient care and more efficient resource utilization.

To this end, the addition of community paramedics may enrich the system that currently manages these patients. Paramedics are a highly-trained group of prehospital practitioners certified in both basic and advanced life support care who work under the medical delegation of base hospital physicians. Paramedics are mobile, community-based practitioners accessible 24 hours a day, who are efficient and effective in managing emergencies and providing comprehensive care in the out-of-hospital environment [12]. Paramedics are the first, and sometimes only, point of contact for many in the community for disease-related exacerbations/symptomatology. They are able to identify subtle signs of potentially life-threatening issues, and provide comprehensive care as per medical directives or reach out to on-call physicians to address issues at the bedside before they become emergencies.

The integration of community paramedics into health care models has attracted international attention. Studies in the United Kingdom, Australia and the United States have shown that community paramedic implementation is feasible, safe and effective while at the same time improving satisfaction of patients and practitioners and minimizing health care costs [13]. Despite this, there has been minimal adoption of community paramedic programs in Canada. While the evidence supporting community paramedicine is promising a comprehensive systematic review identified only a single randomized controlled trial (RCT) from the United Kingdom that evaluated the efficacy of community paramedics [14]. By combining in-home visits by community paramedics with physician oversight and integration with existing community resources, the Expanding Paramedicine in the Community (EPIC) study will provide an innovative chronic care model in order to maximize patient care by allotting available resources in a tiered delivery system.

We propose to perform a randomized controlled trial to answer the following question: does expanding paramedic scope of practice to include chronic disease management, characterized by home visits to facilitate the assessment and treatment of patients under the medical delegation of the primary care physician, reduce the rate of acute care hospitalization?

## Methods/Design

This stratified, randomized controlled trial will examine the effectiveness of a community paramedicine intervention in reducing hospital admission among family health team patients diagnosed with either COPD, HF or DM. We consider our trial to be pragmatic [15] for the following reasons: (1) the patient populations will be broad, targeting patients at high-risk, with few exclusion criteria; (2) the intervention will be implemented in a ‘usual’ practice setting; (3) the intervention will be flexible, and may be adapted according to identified needs over the study period; (4) the outcomes are patient-centered; and (5) the trial results will be of interest to decision-makers [15, 16]. The trial has received research ethics board approval from St. Michael’s Hospital and Markham Stouffville Hospital (Research Ethics Board # 13-086). See Additional files 1 and 2.

### Setting

The regional municipality of York is a geographically diverse region in southern Ontario with a mix of rural and suburban centers and a population of just over 1 million residents. York Region Emergency Medical Services (EMS) is the sole provider of 911 medical services in York Region with both primary care paramedics and advanced care paramedics who are certified through the Ministry of Health and Long-Term Care (MOHLTC). They operate under the medical oversight of physicians from a single base hospital (Central East Prehospital Care Program) and are employed to provide medical care and transportation services within the region.

Patients for this study will be recruited from the Markham Family Health Team and the Health For All Family Health Team, the two largest family health teams in York Region, each with over 5,000 subscribing adult patients.

### Patient population

Patients of the participating family health teams diagnosed with either HF, COPD or DM will be screened for potential study eligibility by their primary care physician by applying search filters to the patients’ electronic medical records (EMR). Eligibility criteria are listed in Table 1. Patients will be deemed to be high-risk at the discretion of the primary care physician, based on (i) prior patterns of health care use, (ii) test results, (iii) compliance and (iv) clinical *gestalt*. Enrolled patients will be confirmed to be high-risk for admission by determining their rates of hospital admission over the 3 years prior to study enrollment, through linkage with the Institute for Clinical Evaluative Sciences (ICES) databases. Rates of admission will then be compared to previous literature to determine patients who are high-risk.

**Table 1 Tab1:** **Study eligibility criteria**

Eligibility criteria	Ineligibility criteria
Patients are eligible if:	Patients are ineligible if:
• They are residents of the region of York	• They are residents of long-term care facilities
• They are 18 years of age or older	• They have cognitive impairment, uncontrolled psychiatric disease or language barriers that would make it difficult to understand the consent and communicate with the paramedic during the scheduled visits, unless the individual with power of attorney for personal care consented and agreed to be at each visit
• They have been diagnosed (at any point in time prior to enrollment) with, and currently receiving treatment for COPD, HF, or DM	
• They are identified by the Family Health Care Team as being at high-risk for hospital admission	

### Recruitment and randomization

Eligible patients will be contacted by their family physician and given multiple opportunities to provide their consent to participate. Enrollment will employ a modified Dillman method [17] with prepaid postage response cards. All patients will be consented using exactly the same process prior to randomization. See Additional files 3 and 4.A block stratified randomization procedure will be used to randomize eligible, consenting patients to treatment or control groups (1:1 ratio). Randomization will occur using a computer generated randomized number sequence allocated by block based on disease, using variable block sizes to avoid substantial imbalances in the number of patients assigned to each group (Figure 1) and to ensure the three disease groups are represented in the intervention or control (usual care) group. Stratification will balance differences in disease characteristics, which may influence the primary outcomes. Should patients have multiple diagnoses, patients with HF will be categorized HF regardless of the other diagnoses and patients with both COPD and DM will be categorized as COPD. Categorization is based on the prevalence of disease previously noted in a subset of patients in which the number of patients diagnosed as having HF was markedly reduced. A preliminary feasibility sample of cases from within the two family health care teams identified 548 patients: 74 COPD patients, 417 DM patients, and 31 HF patients. One patient had all 3 conditions, 17 had diabetes and HF, 1 had HF and COPD and finally 7 patients had both diabetes and COPD. Informed consent will be obtained from all patients prior to enrollment in the EPIC study. Patient recruitment will occur over a 1-year period. Based upon the preliminary feasibility sample and the sample size calculation required to detect a 15% difference in our primary outcome, this will be sufficient time to enroll the required number of patients.

**Figure 1 Fig1:**
[figure not shown]


Patients randomized to the control group will continue to receive usual care from their family health care team. Usual care includes physician assessment and treatment and periodic augmentation of care in the community (CCAC case manager or nurse practitioner) at the discretion of the treating physician.

### Considerations to reduce bias

Due to the intended treatment plan it is not possible to blind paramedics, clinicians or research personnel to treatment assignment. To help minimize selection bias, randomization will occur via a computer-generated random number formulation. Detection bias will be minimized through linkage to copies of province-wide administrative datasets held at ICES. Ascertainment bias will be controlled by using objective clinical outcomes that are not under the control of the paramedic or the family health care team (for example, hospital admission, length of stay, death). Attrition bias is avoided as we are using health outcomes that are routinely measured and housed as administrative data points, and using a primary intention-to-treat (ITT) analysis will minimize the potential bias due to patient withdrawal, dropout or study protocol violations. Contamination bias will be reduced as eligible patients from the same family will be assigned to the first family member’s randomly assigned treatment group. Missing data will be minimized through point of care logic and error checks, built-in data management reports run weekly and timely oversight by study staff; however, any remaining missing data will be dealt with using multiple imputation. The statistical measures of our data management system are published [18]; there is > 90% agreement in the variables of interest common to all cases with moderate or excellent kappa (0.65 to 0.87).

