### Proposed primary and secondary outcome measures

The primary outcome of this trial is the number of hospitalizations per patient after one year of study enrollment. Secondary outcomes will be measures of health system utilization at 1-year (reported as all cause and disease specific) and will include the following:Calls to 911 (regardless of whether patient was transported to hospital)Visits to the participating family health team clinics and any after-hours clinicsLength of stay in hospital if admittedMortalityOverall health status assessment using the (Euroqol-5D 3L) EQ-5D-3L measured at baseline and one year after study enrollment [19, 20]Measures of intervention compliance and safety (that is completed assessments and visits and protocol violations identified by physician review of EMR)Cost-effectiveness analysis for this model of care

The family health team electronic patient record data will be linked via the health card number to province-wide administrative health datasets held at the ICES, a section 45 Prescribed Entity under Ontario’s Personal Health Information Protection Act. Health services data at ICES represent ‘transactions’ of health care utilization, such as inpatient/outpatient hospital utilization, emergency room and other ambulatory clinic visits, drug claims for patients 65 and older, claims for physician services in any setting, and others. Linkage to the ICES administrative databases requires use of the Ontario health card number for each subject; following linkage, only the unique ICES encrypted identifier will remain on the files used for analysis. Linkage will allow us to obtain a more comprehensive view of specific health system utilization than could be achieved with unlinked data. Many disease-specific codes have been validated in ICES’ databases [21–23].

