Patients will be asked about health-related quality of life using the EQ-5D-3 L, [20] a validated measure of quality-adjusted life years (QALY). QALY, a preference-based utility measure, incorporates both length of life and quality of life into a single measure. To estimate QALYs, we will convert EQ-5D data collected in the study to utility score using a validated algorithm [19] so no additional data collection will be required. Health-related quality of life assessments will be performed at baseline and 1-year after study enrollment. Assessments will be performed by the community paramedics for patients enrolled in the intervention cohort and by the patients’ primary care physicians in the control cohort.

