#### II. Data abstraction

Trained data abstractors will enter data from patients’ hospital visits into the EMR. They will be trained by the study staff and complete all the necessary privacy and confidentiality paperwork prior to beginning data abstraction. Patient data will be collected at each encounter with the community paramedic, both scheduled and unscheduled. Data from the paramedic reports and family health team EMRs will be abstracted and manually entered into the database housed at St. Michael’s Hospital on a continual basis throughout the study in real time. Outcome data (that is emergency department (ED) visits, hospital admissions, calls to 911) will be collected at study completion for each patient.

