### Outcome analyses

The MITT or efficacy population will consist of all eligible randomized patients who met all eligibility criteria and who received the full study protocol (4 scheduled paramedic visits over a 1-year period or patients randomized to the control group who remained in the study for the full 1-year period). Furthermore, this trial is intended to target patients with chronic disease who are at high-risk for admission to hospital. However, initial patient enrollment into the study was based upon family physician estimation of patient risk; therefore there is a possibility that some patients enrolled in the study do not represent a high-risk group for hospital admission. Patients enrolled in the trial will have their risk of admission assessed based on their actual rates of admission over the previous 3 years. This information will be gathered through linkage with the ICES databases. Cut-off values for low, medium and high-risk categories will be calculated based on a review of the literature and clinical expertise. Only those patients who are determined to be high-risk will be included in the MITT analysis. Conversely, the ITT or effectiveness population includes all patients randomized regardless of their eligibility, adherence to study protocol or calculated risk of admission.

The primary analysis will be done using an ITT analysis. Baseline characteristics of patients in the intervention and control groups within each disease-specific group will be reported using descriptive statistics, mean/SD or median/IQR for continuous variables and count/percent for categorical as appropriate. Tests of significance will be performed using *t*-tests or Wilcoxon rank-sum test for continuous variables and chi-square or Fisher’s exact test (expected counts < 5) for categorical variables as appropriate. Two-sided *P*-value < 0.05 will be used to determine significant differences in baseline characteristics. These analyses are useful not only to assess the comparability of the treatment group but also to describe the sample of subjects who entered the trial. Test of normality for each variable will be determined using the Shapiro-Wilk test *P*-value < 0.05. All tests will be two-sided and carried out at a significance level at 5%.

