The primary outcome, number of hospital admissions over 1 year will be compared by group using both Poisson regression and negative binomial regression analyses. The goodness of fit of both models will be evaluated using Akaike’s information criterion (AIC) statistics. If, in spite of randomization, differences in baseline characteristics are found using bivariate analytical strategies, these variables will be included in the regression model. Multiple imputation algorithms will be developed in order to determine values for any missing data points [30].

The secondary outcome measures, which are largely count measures, will be compared between control and intervention groups using similar Poisson regression and negative binomial models. The proportion of patients who die during the study period will be compared for the intervention and control groups within each disease-specific group using chi-square tests as well as a logistic regression model, adjusting for any potential confounding variables as appropriate.

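### The treatment plan is given as the reason that no research personnel can be blinded, but that reason does not reach those analysing linked administrative outcomes, and several analysis choices are still open

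*Protocol article*

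**What the plan says.** The blinding statement is in Considerations to reduce bias: "it is not possible to blind paramedics, clinicians or research personnel to treatment assignment". The reason opens the same sentence: "Due to the intended treatment plan it is not possible to blind". Analysts are neither named nor excepted. The section then relies on other protections, chiefly administrative data: "Detection bias will be minimized through linkage to copies of province-wide administrative datasets held at ICES". It names hospital admission, length of stay and death as examples of objective outcomes.

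On the analysis files, Proposed primary and secondary outcome measures says that after linkage "only the unique ICES encrypted identifier will remain on the files used for analysis".

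The following choices are left open:

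- **MITT risk categories** (Outcome analyses): "Cut-off values for low, medium and high-risk categories will be calculated based on a review of the literature and clinical expertise". No values are given.
- **Imputation** (Outcome analyses): the algorithms are still to be developed.
- **Mortality model** (Outcome analyses): logistic regression, "adjusting for any potential confounding variables as appropriate".
- **Count model** (Outcome analyses): Poisson and negative binomial are both fitted and their fit compared by AIC. The text does not say that the lower AIC decides which result is reported as primary.
- **Cost model** (Economic analysis): regression adjusting for potential confounders, with patient characteristics given only as an example.

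**The concern.** In an open trial, masking the people who make analysis decisions is one of the few blinding measures left, and it costs little. A statement that no research personnel can be blinded, read literally, gives it up. The stated reason does not justify that for anyone who works only on linked files.

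What is at stake is direction. Someone who knows which arm is the intervention can lean, even unknowingly, towards the cut-off, imputation model or covariate set that favours it. Someone who sees only A and B cannot. The bias section deals with selection, detection, ascertainment, attrition and contamination, but not with bias at the analysis stage.

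**Working it through.** **1. The reason set against the people it covers.** The treatment plan is a series of home visits.

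| Group | Does the treatment plan reveal the arm? |
|---|---|
| Paramedics, family physicians | Yes, they deliver or oversee the care |
| Staff handling visit data or paramedic reports | Yes |
| EQ-5D-3L assessors | Yes, the assessor differs by arm: "Assessments will be performed by the community paramedics for patients enrolled in the intervention cohort and by the patients’ primary care physicians in the control" arm |
| Analysts of linked admissions, length of stay, death | Not through the treatment plan, if the arm is coded and visit variables are held apart |

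Only the last row falls outside the stated reason.

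**2. Which outcomes this covers.** Not all of them. EQ-5D-3L is collected by unmasked assessors, and compliance and safety come from record review. Hospital data also have a second route: "Trained data abstractors will enter data from patients’ hospital visits into the EMR". The argument is confined to the linked administrative outcomes.

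**3. How open each choice is.** Covariates enter the primary model when baseline differs at two-sided P < 0.05. That rule is mechanical and runs equally well on A/B codes. AIC is mechanical too, provided that it binds. Cut-offs, imputation, mortality adjustment and cost confounders have no mechanical rule in the article.

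**4. The sample size is unaffected.** Inputs from Sample size are rate ratio 0.85, baseline rate 1.85, phi 1.0, R-squared 0.05 and 80% power; the two-sided 5% level is from Outcome analyses. With 1:1 allocation, V0 = 4 and V1 = 2 + 2/0.85 = 4.353:

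N = (1.960 × √4 + 0.842 × √4.353)² / (1.85 × (ln 0.85)² × 0.95) ≈ 694

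The article states 695, so the figure reproduces. Masking enters nowhere in it.

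**5. What masking can and cannot do.** An illustrative null simulation was run with 348 per arm, mean 1.85 and 2,000 trials per row. The dispersion values are assumed. The table gives two-sided rejection rates at the 5% level.

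| Negative binomial dispersion | Poisson always | Model chosen by AIC | Smaller P of the two |
|---|---|---|---|
| 0 | 4.9% | 4.8% | 4.9% |
| 0.25 | 11.0% | 5.6% | 11.0% |
| 0.5 | 15.3% | 4.4% | 15.3% |
| 1.0 | 24.6% | 5.2% | 24.6% |

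The Monte Carlo standard error near 5% is √(0.05 × 0.95/2000) ≈ 0.5 points. A binding AIC rule holds the error near 5% even with the arm in view. Picking the smaller P does not require knowing which arm is which, so a masked analyst could produce the last column as well. The lock removes searching among models; A/B coding removes only steering towards a particular arm. The table therefore separates the two measures and does not give the size of a masking effect.

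**The case against.** The strongest case against has four parts.

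- **The article does not mention analysts.** Research personnel may simply mean staff who enrol, schedule and abstract. A reader might infer that analysis decisions will be made with the arm in view, but no section says who runs the analysis or whether the arm label is open. Analyst masking is often left to an analysis plan, which is not shown here. This stands: the absence of a masking procedure is no finding. What remains is that the sentence as printed is wider than its reason, and a later plan that masked analysts would conflict with its literal wording.
- **The encrypted identifier concerns privacy.** A reader might take de-identified files to be masked, or ready for masking. The documents do not support that. This stands; the identifier is no evidence either way about the arm label.
- **Most open choices are rule-bound or peripheral.** The MITT set is a sensitivity analysis, and its cut-offs are to come from literature and clinical expertise and be applied to admissions before enrolment. The open-ended adjustment concerns mortality, a secondary outcome. The alternative cost estimators are offered to examine assumptions. Little missingness is expected in administrative outcomes. This largely stands and sets the weight of the point.
- **Error inflation from trying several models is not a cost of open labels.** A reader might attach such a figure here. It would measure lack of prespecification, as step 5 of the working shows. This stands in full.

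**Conclusion.** The point holds in a limited form. The article's reason for not blinding does not extend to those who analyse linked administrative outcomes, and the sentence should not cover them. It is not shown that analysts will see the arm or that any choice will be steered. The conclusion rests on two assumptions: that research personnel, read at face value, includes analysts, and that the arm can be coded on the linked file once visit-related variables are held apart.

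No stated figure changes; the sample size stays at 695. The documents give no basis for putting a number on the gain from masking. This is a minor, good-practice improvement to a trial whose primary analysis is intention-to-treat on an objective outcome.

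**What to change.** In Considerations to reduce bias, limit the impossibility statement to paramedics, clinicians and visit-facing staff. Add that analysts, and those who set the MITT risk cut-offs, imputation models, covariates, count model and cost model, work with arms coded A/B until these choices are locked and dated. In Outcome analyses, say whether the lower AIC decides the reported count model. The lock matters as much as the coding, because coding alone does not stop a search among models.

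The cost is wording, an existing staff member to hold the code, and one separate file. Paramedic-visit, compliance, EQ-5D assessor and intervention-cost variables reveal the arm and must stay in that file until the lock. Two steps therefore have to wait. One is the visit-completion part of the MITT set, which is defined by four scheduled visits in one arm and by a full year in the study in the other. The other is the final cost totals, which include the cost of the intervention.

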### Sample size

The proposed sample size is based on yearly hospitalization rates in Ontario of 296/100,000 for HF, [24] 632/100,000 for COPD [25] and 67/100,000 for DM [26] and 1-year mortality rates of 10% for HF, [27] 4.4% for COPD [28] and 8.2% for DM [29]. A Poisson regression with a sample of 695 (348 per group) achieves 80% power at a 0.05 significance level to detect a response rate ratio of at least 0.85 between groups (intervention and control) given a baseline rate of 1.85 and an assumed phi (over-dispersion parameter) of 1.0. The sample size was adjusted since a multiple regression of the covariate of interest on the other covariates in the Poisson regression is expected to have an R-squared of 0.05. We believe this to be sufficient power to detect a clinically relevant improvement of 15% in hospital admission rates. The proposed sample size calculation will be confirmed by using the baseline rates of admission as determined through ICES for patients enrolled in the EPIC study.

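### Relatives who enrol after the first family member can join with their arm already known, and neither the sample size nor the stated models allow for allocation by family

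*Protocol article*

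**What the plan says.** The family rule stands under Considerations to reduce bias, as a guard against contamination: "eligible patients from the same family will be assigned to the first family" member's arm. The same section concedes that "it is not possible to blind paramedics, clinicians or research personnel to treatment assignment".

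Recruitment and randomization describes a 1:1 procedure for individual consenting patients, in variable blocks within disease strata. It has no family exception. On the order of events it says "All patients will be consented using exactly the same process prior to randomization", and on timing "Patient recruitment will occur over a 1-year period". It does not say that eligible relatives must decide on consent before the first of them is randomised.

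Eligibility depends partly on judgement. Under Patient population, "Patients will be deemed to be high-risk at the discretion of the primary care physician", and clinical impression is one of the listed grounds. The family physician also makes the approach for consent.

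Under Sample size, "a sample of 695 (348 per group) achieves 80% power at a 0.05 significance level", with an over-dispersion parameter of 1.0 and no design effect. Outcome analyses compares admissions by group with Poisson and negative binomial regression and adds only covariates found to differ at baseline. No family or household term is named.

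**The concern.** A second or later family member has no randomisation of their own. If that person is identified, judged high-risk or asked for consent after the first member has been allocated, the arm can be known to the physician, the study staff and the family. The computer-generated sequence, which the article relies on against selection bias, then gives that patient no protection. A relative in a household that already receives paramedic visits may be more, or differently, inclined to join than one in a control household. A physician who knows the arm may also judge risk differently. Intention-to-treat analysis does not correct selective entry, and neither do objective administrative outcomes.

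There are two further consequences. Patients from one family share an arm and probably some of their admission risk, so a variance estimate that assumes independent patients is somewhat too small. And a relative in a different disease stratum is allocated outside that stratum's blocks.

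**Working it through.** **Step 1. What the stated sample size assumes.** The inputs come from Sample size and Outcome analyses: rate ratio 0.85, baseline rate 1.85, phi 1.0, R-squared 0.05, 80% power, two-sided 5%. The Poisson-regression formula for a binary covariate split 1:1 is

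N = phi × [z(0.975) × √4 + z(0.80) × √(2 + 2/RR)]² / (rate × (ln RR)²) / (1 − R²)

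- Numerator: (1.960 × 2 + 0.8416 × 2.086)² = 5.676² = 32.22
- Denominator: 1.85 × (−0.1625)² = 0.04886
- Ratio: 659.3. Divided by 0.95: 694.0

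The article states 695, so the figure reproduces, with power 80.05% at N = 695. It does so as a calculation for independent patients with no design effect.

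**Step 2. Clustering by family.** Let f be the share of patients enrolled as one of a two-member family. Then design effect = 1 + f × ICC, and true alpha when clustering is ignored = 2 × [1 − Φ(1.96/√DE)]. The article gives neither f nor the ICC, so both are assumed.

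| f | ICC | Design effect | True alpha | N to keep 80% power | Power at 695 |
|---|---|---|---|---|---|
| 10% | 0.1 | 1.01 | 0.051 | 702 | 79.7% |
| 10% | 0.3 | 1.03 | 0.054 | 716 | 78.9% |
| 20% | 0.2 | 1.04 | 0.055 | 723 | 78.5% |
| 30% | 0.1 | 1.03 | 0.054 | 716 | 78.9% |
| 30% | 0.3 | 1.09 | 0.060 | 758 | 76.7% |

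The last two columns apply when the analysis does allow for clustering. The negative binomial dispersion parameter does not do this: it describes variation between patients, not correlation within a family.

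**Step 3. Selective entry.** In a two-member family only the second member inherits an arm, so the inheriting share is f/2: 5–15% of patients for f = 10–30%. Assume that inheritors in the intervention arm have, through selection alone, a 20% lower admission rate than other patients there, and that inheritors in the control arm do not differ. The intervention-arm rate then shifts by (f/2) × 0.20:

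- f = 10%: 0.05 × 0.20 = 1%
- f = 30%: 0.15 × 0.20 = 3%

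Against the 15% target this is 1/15 to 3/15, or about 7–20% of the effect sought. The 20% and its direction are illustrative; nothing in the article supports a particular value.

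**The case against.** **Timing.** It is tempting to infer that every later relative's arm is known before approach. The article does not say so. Trial status describes a list from the medical-record search, then physician review, then 210 of 548 patients (38.4%) consented and randomised over several weeks. Relatives who all consented before the first of them was randomised would be concealed. This stands, and it limits the point to relatives who enrol afterwards. The text leaves that route open for a year.

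**Contradiction.** A reader might see the family rule as contradicting the statement that all patients consent by one process before randomisation. It need not. A relative can consent by the same process and then receive the family's arm. The recruitment section omits the exception rather than denying it.

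**Analysis detail.** Clustered standard errors are often left to a statistical analysis plan, and one may exist. That these patients will be analysed as independent is therefore an inference from the stated models, not a stated intention. The sample size is fixed in the article, however, and no analysis plan can restore concealment lost at enrolment.

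**Size.** The assumed range for f may be generous. With 38.4% consenting, and relatives consenting independently, f = 30% would need 0.30/0.384 = 78% of eligible patients to have an eligible relative, and f = 10% would need 26%. Consent that runs in families would lower these figures. A larger selection shift, such as 4%, would need 20% of patients to inherit their arm, hence 40% in pairs, which is beyond the range used here.

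**Safeguards.** Admission rates over the three prior years are obtained, baseline differences found on testing enter the model, and the MITT sensitivity analysis keeps only confirmed high-risk patients. These help, but a shift of 1–3% would rarely be flagged. If the prior rate were also 1.85 a year, each arm would have about 348 × 1.85 × 3 = 1,931 prior admissions. The standard error of the log rate ratio would then be about √(2/1,931) = 0.032, and a 3% shift is less than one standard error. The article itself acknowledges a modest remaining threat of selection bias.

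**Purpose.** Keeping families in one arm is a sensible guard against contamination. That stands, and the fix keeps it.

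**Conclusion.** The point holds in a limited form. The rule as written lets a relative who enrols after the first member do so with the arm known, so concealment is not assured for that relative. It also makes allocation clustered by family, for which the sample size and the stated models make no allowance.

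The clustering effect is small: a design effect of 1.01–1.09 and a true alpha of about 0.051–0.06, if 10–30% of patients are in two-member families and the ICC is 0.1–0.3. Selective entry matters more, because a larger sample does not remove it. Its illustrative size is a 1–3% shift in the intervention-arm rate. All of these inputs are assumptions, but the gap in concealment does not depend on them. The article does not show that late entry of relatives has happened, or how often it would. The change is worth making because it is cheap and keeps the contamination safeguard.

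**What to change.** - **Enrolment.** Use the medical-record list to identify eligible members of the same family. Settle eligibility and consent for all of them, then randomise the family once. State the family exception, and how a family with members in different disease strata is placed, in the recruitment section.
- **Data.** Create a family identifier and keep it through the ICES linkage. The article says that after linkage only the encrypted ICES identifier stays on the analysis files, so this must be arranged beforehand.
- **Analysis.** Use family-clustered robust standard errors in the primary and secondary models. Add a sensitivity analysis that excludes members who joined after their family's arm was allocated. Report the number of multi-member families and of late joiners by arm.

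The cost is a family check before randomisation, a slight delay for multi-member families, and marginally wider confidence intervals.
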